## 2. Protocol Summary

- 1) Study Design: This is randomized phase II clinical trial

- 2) Purpose: Evaluation of anti-tumor efficacy against postoperative intra and extra hepatic metastasis and toxicity of Antineoplaston A10 and AS2-1 in colorectal cancer.
- 3) Eligibility: Eligible patients had histologically confirmed metastatic colorectal adenocarcinoma to the liver. Patients were treated with R0 resection of liver metastases and/or complete ablation by radio frequency interstitial ablation therapy between April 1998 and August 2004 at Kurume University Hospital.
- 4) Treatment: In control group, patients received HAI with 5-FU at a dose of 1000 mg/m^2 for 4 hours weekly or biweekly after hepatectomy until the cumulative dose reached up to 15,000 mg.  
In Antineoplaston group, Antineoplaston A10-Injection and AS2-1 were administered from day 15 after liver surgery in addition to HAI same as in control group with a starting dose of 30 g/day of intravenous A10-Injection using a pump system to maximum dose of 100 g/day for more than 3 days. After completion of the i.v. administration of A10-Injection for a week, 10 g/day of AS2-1 was administered orally for 1 year.
- 5) Primary Study Endpoints: The efficacy and safety endpoints will be Cause-specific survival rate, Disease free survival rate, Degree of recurrence, frequency, severity of adverse events.
- 6) Total number of patients: a total of 50 patients will be enrolled with 25 patients randomized to one of two treatment groups.
- 7) Duration of Study: The study will conduct from April 1998 to December 2004 and the prognosis of patients will be followed for at least 5 years.

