**Antineoplaston A10 Injection and AS2-1**

On 15th day after liver surgery Antineoplaston A10 Injection (30 g/day) starts to be infused through the catheter instituted in great vein and increase the dose up to maximum 100 g/day and keep this dose for 3 days. Then Antineoplaston AS2-1 10 g/day (at breakfast, lunch, dinner and before sleep) starts to be administered and continued for one year.

8. Randomization

Eligible patients are randomly assigned to receive systemic antineoplastons plus 5-FU HAI (AN arm) or 5-FU alone (control arm) by minimization method using number of metastases (1-3 vs >4) and presence or absence of prior extra-hepatic metastases which were removed completely at the time of surgery.

9. Drugs during the study period

No other anti-cancer drugs should be used during the study period.

No limitation of use of anti-histamine or digestive medication is applied.

10. Therapy during the study period

Chemotherapy, immunotherapy and radiotherapy are not conducted during the study period. When any of those therapies has conducted with un-avoidable reason the content of the conducted therapy, when it has conducted and details of course history should be recorded.

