- 4) Unable to administer testing drugs due to adverse effects
- 5) Patient or family want to withdraw from the study
- 6) Unable to follow patient
- 7) When attendant investigator judge not to continue the study

In the interrupted cases, clinical observation, physical examination and clinical tests should continue as scheduled to evaluate the efficacy and toxicity of testing drugs.

In the interrupted cases who have not visited hospital, an effort should be paid to follow up the patients to clarify the prognosis and the reason why not visiting hospital.

13. Registered patients in the study are categorized into appropriate, inappropriate, perfectly treated, imperfectly treated and appropriate perfectly treated by the standard of Japanese Cancer Patient Follow up Committee in Japanese Society of Cancer Therapy.

14. Evaluation of efficacy

Efficacy of the testing drug should be evaluated by comparing cause specific survival, time to intra-hepatic recurrence, degree of extension of recurrence and time to extra-hepatic recurrence between Antineoplatstons treated group and control group.

15. Serious adverse effects during the study should be reported immediately to the

safety committee and treated properly. The safety committee of this study consists of principal investigator and study investigators. The safety committee should be open to patient's contact 24 hours a day.

16. Follow up

Treatment of patient disease after the study completed will be depending on attendant physician's decision, the prognosis of patient will be followed up to 5 years after study treatment.

17. Sample size

Statistical consideration for obtaining significance at 5 years survival needs 25 patients in each group making total 50 patients.

18. Time to start the study

The study starts from April, 1998 for 10 years.

19. End of the study

The study will ends enrollment as soon as 50 patients finish the study treatment.

20. Recording

- 1) Recording should be written in black
- 2) Correction of description must be done by X mark or two lines with signature who made correction. The date and reason for correction must be noted if the correction is major and serious.

21. Management of testing drugs

Testing drugs are managed by a study investigator who takes care of drug management.

22. Organization of conducting this study

Lower Gastrointestinal Group in Department of Surgery, Kurume University, School of Medicine

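### Cause-specific survival is the only named survival endpoint, with no rule for assigning cause of death; all-cause survival is never named, and disease-free survival is undefined and missing from Section 14

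*Protocol*

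**What the plan says.** Section 2, item 5 of the protocol lists the primary endpoints: "The efficacy and safety endpoints will be Cause-specific survival rate, Disease free survival rate, Degree of recurrence, frequency, severity of adverse events". Section 14 describes the efficacy comparison differently: "Efficacy of the testing drug should be evaluated by comparing cause specific survival, time to intra-hepatic recurrence", then how far recurrence extends and time to extra-hepatic recurrence, antineoplaston group against control. Disease-free survival appears in the first list and not in the second. The two site-specific recurrence times appear in the second and not in the first. Disease-free survival is not defined in either place.

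Section 17 gives the basis for the sample size: "Statistical consideration for obtaining significance at 5 years survival needs 25 patients in each group making total 50 patients". It does not say whether survival there is all-cause or cause-specific.

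Sections 7 and 8 give the antineoplaston arm a central-vein infusion and a year of oral drug on top of hepatic arterial 5-FU; the control arm has 5-FU alone. No placebo or blinding is described. The only committee mentioned is in Section 15: "The safety committee of this study consists of principal investigator and study investigators". No section says who assigns cause of death, or by what rule.

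**The concern.** In its ordinary sense, cause-specific survival counts deaths from the cancer and treats other deaths as censored. That causes two difficulties here.

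First, the arms differ by an added treatment. If that treatment caused a death, the survival comparison as named would not record it as an event, so the endpoint is insensitive to a fatal harm that could arise in one arm only.

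Second, each death has to be classified. With no placebo described, and no stated rule or independent body, the classification probably falls to people who know the arm. Vital status needs no such judgement, and the 5-year follow-up of prognosis in Section 16 should supply it in any case.

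A well-defined disease-free survival would largely meet the first difficulty. The protocol leaves it undefined and omits it from the section that says how efficacy is judged.

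**Working it through.** **The plan's own figure.** Section 17 gives 25 per arm but no alpha, power, survival rates or dropout, so the figure can only be back-solved. The usual formula is n = [1.96·√(2p̄q̄) + 0.842·√(p₁q₁ + p₂q₂)]² / (p₂ − p₁)², for assumed two-sided 0.05 and 80% power. With p₁ = 0.40 and p₂ = 0.781 it gives (1.363 + 0.540)² / 0.145 ≈ 25. For control rates of 20% to 50%, 25 per arm corresponds to a gain of about 36 to 39 points. This applies equally to either kind of survival, so the number does not show which one Section 17 means.

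**How far one re-attributed death moves the estimate.** Take 25 patients, complete 5-year follow-up and 10 deaths (assumed).
- All-cause: 15/25 = 60.0%.
- Earliest death censored: the other 9 fall among 24 at risk, 15/24 = 62.5%, a shift of 2.5 points.
- Latest death censored: 16/25 = 64.0%, a shift of 4.0 points, the maximum (1/25).
- Two deaths: 15/23 = 65.2% if the two earliest are censored (5.2 points), 17/25 = 68.0% if the two latest (8 points).

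**Effect on significance, re-attributed death counted as a survivor.** Fisher exact test, deaths in antineoplaston v control arm, 25 each:

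| All-cause deaths | p | One antineoplaston death removed | p |
|---|---|---|---|
| 10 v 17 | 0.088 | 9 v 17 | 0.046 |
| 7 v 14 | 0.085 | 6 v 14 | 0.042 |

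This overstates the effect, because cause-specific survival would censor the patient and not turn a death into a 5-year survivor.

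**Effect on significance with censoring.** Log-rank χ² = (O − E)²/V for the antineoplaston arm. Death times are assumed to lie at exponential quantiles, tᵢ = −ln(1 − (i − 0.5)/25)/λ with λ = −ln(1 − d/25)/5 for d deaths in the arm, and survivors are censored at 5 years.

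| Deaths | Analysis | O | E | V | p |
|---|---|---|---|---|---|
| 10 v 17 | all-cause | 10 | 15.18 | 6.60 | 0.044 |
| 10 v 17 | earliest antineoplaston death censored | 9 | 14.67 | 6.35 | 0.024 |
| 10 v 17 | latest antineoplaston death censored | 9 | 14.54 | 6.37 | 0.028 |
| 8 v 14 | all-cause | 8 | 12.00 | 5.43 | 0.086 |
| 8 v 14 | earliest antineoplaston death censored | 7 | 11.49 | 5.18 | 0.048 |
| 8 v 14 | latest antineoplaston death censored | 7 | 11.40 | 5.19 | 0.053 |

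The 10 v 17 result is significant both ways. The 8 v 14 result crosses 0.05 only when the censored death is early.

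**How often it could matter.** Exact binomial enumeration gives the share of significant results (two-sided 0.05) that would be lost by counting one more antineoplaston death. For assumed true 5-year survival of 40% v 60%, 40% v 70% and 40% v 77%, the shares are 34%, 23% and 16% with Fisher's test, and 29%, 19% and 12% with chi-square. These also treat the re-attributed patient as a survivor, so they lean high.

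**The case against.** The stated purpose in Section 2 is anti-tumour efficacy against intra- and extra-hepatic metastasis in a phase II trial, and tumour-specific endpoints suit that purpose. This stands as a reason to keep cause-specific survival, but not as a reason to have no other survival endpoint.

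A reader might go further than the protocol allows in several ways.

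- *That no endpoint counts treatment-related deaths.* Disease-free survival remains a listed primary endpoint, and nothing in Section 14 withdraws it. What can be shown is a mismatch and a missing definition.
- *That fatal harm would be hidden.* Adverse events are among the same primary endpoints, and Section 15 requires immediate reporting of serious ones. Such a death should be recorded, although the survival comparison would still omit it.
- *That the protocol orders such deaths to be censored, or states that the trial is open label.* It does neither. Both are inferences, from the usual meaning of the term and from the absence of a placebo. An analysis plan not shown here may define the handling.
- *That the site-specific recurrence times mishandle death before recurrence.* Handling of competing events is ordinary analysis-plan content.
- *That degree of recurrence is compared only among patients who recur.* Section 14 compares the treatment groups and contains no such restriction.
- *That one re-attributed death overturns the result.* This is true only near the boundary. Sensitivity to a single death is also a property of 50 patients, and an all-cause analysis shares it. Only the dependence on attribution is specific to this endpoint.

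Section 17 may itself mean all-cause survival. In that case the trial is sized on an outcome that its endpoint lists never name, and the sections still need to be reconciled.

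**Conclusion.** The concern holds in limited form. The protocol chooses cause-specific survival as its only named survival endpoint, says nothing on how cause of death is decided, and leaves undefined the one listed endpoint that would usually count every death. The survival comparison can therefore miss deaths attributed to the added treatment, and it depends on judgement that is probably unblinded.

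One re-attributed death is worth at most 4 percentage points in an arm, and 2.5 in the early-death example. It alters significance only for results close to the threshold. The p-values assume two-sided 0.05, 25 per arm, complete follow-up and, for the log-rank figures, exponential death times; the protocol states neither alpha nor rates. This should be fixed. Because disease-free survival and adverse events remain primary endpoints, it falls short of a defect that must be cured before the trial can be interpreted at all.

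**What to change.** - In Section 2 item 5, Section 14 and Section 17, name all-cause survival from randomisation as the survival endpoint, and keep cause-specific survival as supportive.
- Define disease-free survival as time to first recurrence at any site or death from any cause, and carry it into Section 14 so that the two endpoint lists agree.
- State that degree of recurrence is compared over all randomised patients, with 'no recurrence' as the lowest category.

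The cost is protocol wording and a little extra analysis. No new patients, visits or data are needed, since vital status should come from the follow-up already planned in Section 16. The downside is slight noise from deaths unrelated to cancer or treatment.
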